### 2.6. Recruitment

Participants will access the Mental Health Unit through university-based mental health services, including referrals from student support services as well as spontaneous presentation to the outpatient mental health service. Self-referred participants will be eligible for screening and will undergo the same eligibility assessment procedures and inclusion/exclusion criteria as all other potential participants.

Recruitment will be conducted through standardized institutional communication channels, including university-wide emails, the Integrated Academic Activities Management System (SIGAA), and social media announcements. Recruitment materials will describe the study as a randomized clinical trial comparing two brief psychotherapeutic interventions for anxiety and depressive symptoms. To preserve the integrity of study procedures, recruitment materials will not disclose allocation procedures or specific study hypotheses. However, participants will be informed during the consent process that the study includes an experimental psychotherapeutic intervention, in accordance with ethical requirements for informed consent.

Interested participants will be invited to contact the research team and will subsequently undergo eligibility assessment according to the predefined inclusion and exclusion criteria. Eligible participants who provide written informed consent will proceed to randomization and study enrollment.

### 2.7. Randomization and Blinding

Randomization will be performed after eligibility confirmation and informed consent. The allocation sequence will be generated by an independent researcher using a computer-based randomization procedure, stratified by clinical condition.

Allocation concealment will be ensured using sequentially numbered, opaque, sealed envelopes prepared by a researcher not involved in recruitment, assessment, or intervention delivery.

The envelope will be opened immediately before the psychotherapy session by the therapist responsible for intervention delivery. A confidential file linking participant identifiers to randomization codes will be maintained by the independent researcher who generated the allocation sequence and stored securely in a password-protected cloud system.

Participants will be informed that two psychotherapeutic approaches are being compared, without disclosure of allocation or study hypotheses, to minimize expectancy bias. Distinct researchers will be responsible for randomization, intervention delivery, outcome assessment, biomarker analysis, and statistical analysis, with no cross-access to allocation data during the trial.

The same procedures will be replicated in Phase 2.

### 2.8. Roles and Confidentiality

The study will be conducted at the Onofre Lopes University Hospital (EBSERH), Federal University of Rio Grande do Norte, using institutional clinical infrastructure without additional costs to participants. As there is no external commercial or financial sponsor, no external party is involved in study design, data collection, analysis, interpretation of data, manuscript preparation, or publication decisions. The investigators retain full scientific independence.

Allocation confidentiality will be managed by a designated investigator with restricted access to the randomization key, which will be securely stored in a password-protected file. This role is strictly administrative and limited to data governance.

Clinical interviews for eligibility confirmation will be conducted by trained clinical personnel according to DSM-5-TR criteria prior to inclusion.

Biological samples will be processed and stored by a dedicated researcher responsible for the biorepository, using coded identifiers stratified by sex to ensure confidentiality and traceability.

Statistical analysis will be performed by an independent data analyst using de-identified datasets, ensuring separation from clinical and intervention procedures.

Participant data will be coded at enrollment using official documentation. All datasets will be stored in encrypted, password-protected systems managed by the responsible researchers, with identification keys retained by the principal investigator to ensure confidentiality and traceability.

In cases of dropout or exclusion, participants will be retained in the intention-to-treat analysis, with identification keys remaining under the custody of the principal investigator, and all procedures will be duly documented, including reasons for exclusion, with missing data handled using appropriate statistical methods.

Strategies to ensure treatment adherence include institutional communication, structured scheduling, and clear guidance provided at informed consent, with emphasis on confidentiality and protocol compliance.

No Data Monitoring Committee will be established, and no interim analyses are planned due to the low-risk outpatient nature of the study. The study will be supervised by the investigators with clearly defined roles across trial activities. The principal investigator will oversee protocol compliance without involvement in intervention delivery or data analysis.

Therapist Training and Fidelity:

All interventions will be conducted by licensed clinical psychologists working within the public mental health outpatient service of the Onofre Lopes University Hospital (EBSERH), Federal University of Rio Grande do Norte. They have prior clinical experience in the treatment of participants with anxiety and depressive disorders in routine mental health care. Prior to study initiation, therapists will undergo standardized training in both BATF and Brief Focal Psychotherapy protocols, including theoretical orientation, manual-based procedural instruction, supervised practice, and calibration exercises to ensure fidelity to intervention procedures. Therapists will be trained in both intervention protocols and will be capable of delivering either treatment according to randomized allocation procedures. Intervention delivery will strictly follow study allocation procedures.

BATF is a fully manualized and standardized protocol and will be delivered according to a detailed treatment manual, with the aim of minimizing performance and therapeutic allegiance bias. Treatment fidelity will be ensured through structured post-session checklists, ongoing clinical supervision, regular calibration meetings, and strict adherence to intervention manuals. The investigator clinical psychologist will be responsible for therapist training, inter-therapist calibration, and supervision of intervention delivery to ensure consistency in the application of procedural components, with systematic documentation of any protocol deviations.

### 2.9. Data Collection

#### 2.9.1. Blood and Saliva Collection Procedures

Blood samples will be collected using sterile equipment by trained technicians. A total of 30 mL of blood will be collected in the morning, with the volunteer in a fasted state. On the same days and weeks, the volunteer will also perform three saliva collections at home, at the following intervals: 0, 30, and 45 min after waking up. The cortisol collection at awakening is standardized and must be performed immediately upon waking up, using a salivette, with subsequent collections at 30 and 45 min after waking. The volunteer will receive the salivette and detailed instructions the day before the collection.

To enhance adherence to the saliva sampling protocol, participants will receive standardized written and verbal instructions, and sampling times will be clearly explained during training. Participants will be instructed to record the exact time of awakening and each saliva collection using a structured collection log (self-report diary). Additionally, they will be provided with labeled collection materials corresponding to each time point (0, 30, and 45 min) to reduce timing errors. Compliance will be checked upon sample return, and any deviations from the prescribed timing will be documented and considered in sensitivity analyses when appropriate.

Standardized pre-analytical procedures will be implemented to minimize variability in biomarker measurements. Samples will be collected in the morning under fasting conditions. Participants will be instructed to avoid physical exercise within 48 h prior to collection and to ensure at least 7 h of sleep on the night preceding sampling. Acute illness at the time of assessment will result in rescheduling of sample collection when necessary. Information on medication use, menstrual cycle phase, and use of oral contraceptives will be recorded and considered in sensitivity analyses when appropriate. Caffeine and food intake will be controlled through fasting conditions prior to sample collection.

All collected material, both blood and saliva, will be stored in a biorepository at the Human Measures Laboratory of the Center for Biosciences at the Federal University of Rio Grande do Norte (UFRN), and will be used exclusively for the measurement of the described molecules.

#### 2.9.2. Structured Clinical Interview for DSM-5-TR

The Structured Clinical Interview for DSM-5-TR (SCID-5-TR) will be utilized for screening participants for anxiety and depressive disorders and for determining eligibility prior to randomization. This tool is crucial for selecting subsequent clinical assessment instruments and for establishing the participant’s primary clinical condition. The interview will be administered by trained clinical personnel, including licensed psychologists and psychiatrists from the Mental Health Unit of the Onofre Lopes University Hospital. Interviewers have experience in the assessment of anxiety and depressive disorders and will receive standardized training regarding study procedures before participant recruitment. The interview has been translated and adapted into Portuguese.

#### 2.9.3. Montgomery-Åsberg Depression Rating Scale (MADRS)

The MADRS demonstrates high inter-rater reliability, provides an estimate of severity, and is superior to the Hamilton Depression Rating Scale (HAM-D) in differentiating between responders and non-responders to antidepressant treatment [14].

#### 2.9.4. Clinical and Self-Report Assessment Scales

The Hamilton Anxiety Scale (HAM-A) is among the most widely utilized scales and serves as a reference for newer scales [15]. Self-report measures include the PHQ-9 (for depression), the GAD-7 (for anxiety), and the Pittsburgh Sleep Quality Index.

The GAD-7, a screening tool and severity indicator, allows participants to report their level of discomfort related to anxiety over the past two weeks. The PHQ-9, also a screening tool, provides insight into the patient’s perspective on depressive symptoms over the past two weeks [16]. The PHQ-9 is also a reliable and valid measure of depression severity [17].

The Pittsburgh Sleep Quality Index, with its Brazilian version showing high internal consistency and moderate reliability, assesses sleep quality [18]. The inclusion of these comprehensive assessment tools and the focus on sleep quality reflect the study’s commitment to thoroughly evaluating both the psychological and physiological impacts of the interventions [19].

Both instruments have validated Brazilian Portuguese versions with established psychometric properties [20,21]. These scales will be used in conjunction with clinician-administered instruments (MADRS and HAM-A) to provide complementary assessment of anxiety, depression, and sleep quality.

#### 2.9.5. Salivary Biomarkers and Blood Biomarkers

This study will evaluate clinically relevant salivary and blood biomarkers associated with stress response, inflammation, and neurobiological regulation in anxiety and depressive symptoms. Salivary biomarkers assessed in this study include cortisol, glutamate, immunoglobulin A, lysozyme, melatonin, alpha-amylase, chromogranin A, and fibroblast growth factor 2, which have been implicated in stress reactivity, immune modulation, and neuroendocrine dysregulation in affective disorders [22,23,24,25,26,27].

Blood biomarkers assessed in this study include cortisol, pro-BDNF, mature BDNF, sex hormones, dehydroepiandrosterone, C-reactive protein, growth hormone, and glutamate, which have been linked to depression severity, stress regulation, and inflammatory and neuroplasticity pathways [28,29,30,31,32,33,34,35]. In the present study, BDNF (pro-BDNF and mature BDNF) will be assessed exclusively in blood samples.

Given the exploratory nature of these analyses, biomarker outcomes will be interpreted within an integrated systems framework encompassing hypothalamic–pituitary–adrenal (HPA) axis activity, immune-inflammatory signaling, and neuroplasticity mechanisms.

### 2.10. Sample Size

The standard deviation for the Montgomery-Åsberg Depression Rating Scale (MADRS) was estimated to be 11 [36]. The minimal clinically significant difference on the Montgomery-Åsberg Depression Rating Scale (MADRS) is considered to be 5 points. The minimal clinically important difference for the MADRS is not universally established and varies according to the estimation method and study population. Published estimates generally range from approximately 3 to 9 points, with values around 3–6 points considered among the most plausible across different methodological approaches. Therefore, a 5-point difference was adopted as a pragmatic mid-range estimate for sample size calculation purposes [37]. Alpha (α): a classical significance level of 5% is used, commonly applied in health research. A statistical power of 80% (β = 0.20) was adopted, as commonly recommended in health research.

The sample size was calculated based on the change in Montgomery–Åsberg Depression Rating Scale (MADRS) scores from baseline to week 13 (primary outcome). A two-sided significance level of 5% (α = 0.05), statistical power of 80% (β = 0.20), a clinically meaningful difference of 5 points, a standard deviation of 11, and a 1:1 allocation ratio were assumed. The calculation was performed using a two-sample *t*-test for independent means implemented in G*Power version 3.1.9.7. This corresponds to a standardized effect size of Cohen’s d = 0.45.

#### 2.10.1. Sample Size Calculation for Initial Phase

To test the effect of BATF compared to the active comparator group, and to ensure sample homogeneity by clinical condition, the comparison of mean differences between the two groups is conducted. With the given parameters, the required sample size is 77 participants per group, totaling 154 participants. To account for the need to evenly distribute participants, 78 participants per group are necessary, resulting in a total of 156 participants.

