### 2.5. Outcomes

The objective of this study is to evaluate the effects of a brief psychotherapeutic intervention, BATF, compared with Brief Focal Psychotherapy in reducing symptoms of anxiety and depression.

Outcomes include quantitative measures of depressive and anxiety symptoms, sleep quality, and exploratory salivary and blood biomarkers associated with stress, inflammatory processes, and neurobiological function.

The co-primary outcomes for Phase 1 are defined as the change from baseline (Week 0) to Week 13 in symptom severity within each diagnostic stratum, assessed using disorder-specific scales (MADRS for depressive disorder and HAM-A for anxiety disorder).

Clinical diagnoses will be established during baseline psychiatric and clinical evaluation according to DSM-5-TR criteria prior to randomization. Participants will be stratified according to their primary clinical condition (anxiety or depressive disorder) and randomized to one of the two psychotherapeutic interventions. Each participant will be assessed only with the symptom severity scale corresponding to their primary diagnosis.

Secondary outcomes include depressive and anxiety symptom severity assessed using disorder-specific instruments according to participants’ primary clinical condition (PHQ-9 for depressive disorders and GAD-7 for anxiety disorders). Sleep quality, assessed using the Pittsburgh Sleep Quality Index (PSQI), and exploratory biomarker analyses will be performed in all participants.

Exploratory outcomes include salivary and blood biomarkers. Salivary biomarkers include cortisol, glutamate, immunoglobulin A (IgA), lysozyme, melatonin, alpha-amylase, chromogranin A, and fibroblast growth factor 2 (FGF2). Blood biomarkers include cortisol, pro–brain-derived neurotrophic factor (pro-BDNF), mature BDNF, sex hormones, dehydroepiandrosterone (DHEA), C-reactive protein (CRP), growth hormone, and glutamate. Cortisol and glutamate will be assessed in both saliva and blood samples. All biomarkers are pre-specified in the Statistical Analysis Plan and will be considered exploratory and hypothesis-generating.

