#### 2.10.2. Sample Size for Second Phase

The second phase of the clinical trial will require a larger sample size. Upon reaching 156 participants, the initial results comparing the two psychotherapies (experimental and active comparator groups) will be published. The research methodology will remain unchanged, but the second phase aims to assess the effect of condition across four distinct groups (BATF for depression, BATF for anxiety, control for depression, and control for anxiety).

An Analysis of Variance (ANOVA) will be employed for this comparison. The sample size calculation for this phase requires a total of 472 participants. Therefore, an additional 316 participants need to be recruited, with 79 participants in each of the four groups. This requirement accounts for the data from the initial 156 participants, which will be included in the evaluations for the second phase to achieve the total sample size of 472 for comparison across the four groups.

The sample size calculation for Phase 2 was based on a 2 × 2 factorial design with four equally sized groups, assuming balanced allocation across conditions (*n* = 118 per cell in the final sample). The calculation maintained the same statistical assumptions as Phase 1. No formal interim adjustments were planned, and the design assumes complete case availability at the final analysis stage. Importantly, no attrition (dropout) rate was included in the sample size calculation, which may result in reduced effective statistical power if loss to follow-up occurs during the trial.

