### 2.11. Statistical Methods

The primary analysis (Phase 1) will compare BATF versus Brief Focal Psychotherapy in a combined sample of participants with anxiety and/or depressive symptoms, irrespective of diagnostic category (“collapsed” clinical conditions). This analysis represents the primary confirmatory comparison of the trial.

Exploratory subgroup analyses within Phase 1 are pre-specified and will evaluate treatment effects separately in participants with anxiety and depressive symptoms.

The secondary analysis (Phase 2) will examine a pre-specified 2 × 2 factorial analytical framework (intervention × clinical condition), allowing assessment of main and interaction effects across four groups (BATF-depression, BATF-anxiety, control-depression, and control-anxiety), resulting in four analytical cells for the 2 × 2 factorial analysis.

For Phase 1, the primary comparison between BATF and Brief Focal Psychotherapy will be performed using Student’s *t*-test for normally distributed change scores or the Mann–Whitney U test when normality assumptions are not met. The first phase will include 156 participants.

Phase 2 will include a total sample of 472 participants (including participants from Phase 1 plus additional recruited participants). Change scores will be compared across the four predefined groups (BATF-depression, BATF-anxiety, control-depression, and control-anxiety) using one-way analysis of variance (ANOVA) or the Kruskal–Wallis test, as appropriate.

Assessments performed at Week 4 will be used to describe intermediate clinical evolution and may support exploratory analyses of treatment trajectories.

Effect Size Measure: Omega squared (ω^2^); Statistical Significance Level: α = 0.05.

Multiplicity for the co-primary outcomes will be controlled using the Holm–Bonferroni procedure. Secondary and subgroup analyses will be considered exploratory and interpreted accordingly. Exploratory biomarker analyses will apply false discovery rate (FDR) correction according to the Benjamini–Hochberg method.

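### The 80% power in section 2.10 counts 77–78 MADRS change scores per arm, but section 2.5 gives MADRS only to the depression stratum, about 39 per arm in Phase 1

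*Protocol article*

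**What the plan says.** The sizing outcome in section 2.10 is change in "Depression Rating Scale (MADRS) scores from baseline to week 13 (primary outcome"). The inputs are "A two-sided significance level of 5% (α = 0.05), statistical power of 80% (β = 0.20), a clinically meaningful difference of 5 points", with "a standard deviation of 11, and a 1:1 allocation ratio were assumed", in a two-sample t-test. On effect size the section adds: "This corresponds to a standardized effect size of Cohen’s d = 0.45". Section 2.10.1 gives the result: "With the given parameters, the required sample size is 77 participants per group, totaling 154 participants". It then rounds up to 78 per group, 156 in all.

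Section 2.5 defines co-primary outcomes within each diagnostic stratum, MADRS for depressive disorder and HAM-A for anxiety disorder, and states: "Each participant will be assessed only with the symptom severity scale corresponding to their primary diagnosis". Section 2.11 adds: "Multiplicity for the co-primary outcomes will be controlled using the Holm–Bonferroni procedure".

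For Phase 2, section 2.10.2 says that "an additional 316 participants need to be recruited, with 79 participants in each of the four groups", and gives a final size of 118 per cell.

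Sections 2.1, 2.2 and 2.11 describe the Phase 1 primary differently, as one comparison of the two therapies with the clinical conditions collapsed. Section 2.11 also calls the separate anxiety and depression analyses exploratory subgroups.

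**The concern.** The calculation needs a MADRS change score from every one of the 156 Phase 1 participants. Under section 2.5 those in the anxiety stratum have none. The number of MADRS scores per arm is therefore the size of the depression stratum, about half of what was assumed. The significance level does not match either: the calculation uses 0.05 for one test, while section 2.11 shares alpha across two co-primaries.

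Phase 1 is the trial's confirmatory analysis and is to be published once 156 participants are reached. If its MADRS result is null, readers will judge it against a stated 80%. On the section 2.5 definition, a null result would be about as likely as a positive one even if the planned 5-point effect were real.

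**Working it through.** **Inputs.** From section 2.10: difference 5, SD 11, two-sided alpha 0.05, power 80%, 1:1 allocation, two-sample t-test. From section 2.10.1: 77, then 78 per arm. From section 2.10.2: 118 per final cell, of which 79 are newly recruited. From section 2.11: Holm over two co-primaries, so 0.025 at the first step and 0.05 at the second.

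**1. The plan's own figure.** d = 5/11 = 0.4545. Power is the probability that a noncentral t variable, with 2n − 2 degrees of freedom and noncentrality d × √(n/2), exceeds the critical value in absolute size. Solving for 80% gives n = 76.95, so 77 per arm. Power is 80.0% at 77 and 80.5% at 78. The stated figure reproduces.

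**2. MADRS scores available.** 118 − 79 = 39 per cell in Phase 1, which equals 156/4. The depression stratum therefore supplies 39 MADRS change scores per arm.

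**3. Power at 39 per arm.** Noncentrality = 0.4545 × √(39/2) = 2.01, with 76 degrees of freedom.

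| MADRS scores per arm | Power at 0.05 | Power at 0.025 |
|---|---|---|
| 78 (as sized) | 80.5% | 71.7% |
| 47 (60% depression) | 58.7% | 47.3% |
| 39 (implied by section 2.10.2) | 50.9% | 39.5% |
| 31 (40% depression) | 42.1% | 31.2% |

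The rows for 31 and 47 show the range if the strata are unequal. Randomisation is stratified, but the article states no stratum quotas.

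**4. Holm.** The 0.025 column is the first step only. MADRS can also be rejected at 0.05 when HAM-A passes at 0.025. If HAM-A has the same standardised effect and n (an assumption) and the strata are independent:

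- P(reject MADRS) = 0.395 + (0.509 − 0.395) × 0.395 = 0.44
- P(reject at least one co-primary) = 1 − (1 − 0.395)² = 0.63

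**5. Detectable difference and n needed.** With 39 per arm, 80% power needs d = 0.643 at 0.05 or 0.710 at 0.025. Multiplied by 11, that is 7.1 or 7.8 points. Section 2.10 itself puts the most plausible minimal important difference at about 3 to 6 points. To detect 5 points with 80% power, the depression stratum alone would need 77 per arm at 0.05 or 94 per arm at 0.025.

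**6. The collapsed reading.** All 78 per arm contribute, half with MADRS and half with HAM-A. Power is 80.5% only if d = 0.4545 holds for a common standardised score. With equal strata and d = 0.4545 for MADRS, the pooled effect is (0.4545 + d for HAM-A)/2. Illustrative HAM-A values, which are not in the article, give about 65% power at 0.30, 53% at 0.20 and 29% at 0.

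**The case against.** The strongest reply is that the primary is the collapsed comparison. Three sections say so, and section 2.11 calls the stratum analyses exploratory, so no power was promised for them. This stands in part: the 51% and 39% are the power of a confirmatory test only if section 2.5 prevails. It does not rescue the 80% as written. The difference and SD are in MADRS points, no effect is stated for a pooled MADRS/HAM-A score, and a single collapsed test would leave Holm with no co-primaries to adjust.

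Second, 39% is not the power under Holm. That is correct: under the equal-effect assumption it is about 44% for MADRS, with about 63% for at least one co-primary.

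Third, the HAM-A assumptions may be in the analysis plan, which is not shown. Their absence from the article is therefore not held against it. The point is that the sizing stated in the article does not fit the outcome definition stated in the article.

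Fourth, reduced power is already admitted. Section 2.10.2 and the Discussion admit it for dropout only, not for the halving of n by stratum.

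A reader might go further and infer an arithmetic mistake, or conclude that adopting the collapsed test settles the matter with no extra participants. The documents support neither. The 77 is computed correctly, and the second inference needs an effect of about 0.45 in the anxiety stratum, which the article does not give.

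**Conclusion.** The point holds as a mismatch between the endpoint and the population used for sizing. On the section 2.5 co-primaries, the MADRS comparison has about half the information that section 2.10 assumes, and its power falls from the stated 80% to roughly 40–50%, depending on the alpha applied. This rests on the article's own difference and SD, on the 39 per cell implied by section 2.10.2, and on no dropout. A 40% to 60% depression share changes the figures but does not restore 80%. Power for HAM-A cannot be computed from the article.

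On the collapsed reading, the 80% is conditional on an unstated assumption rather than shown to be false. On neither reading is the claim in section 2.10 supported as it stands.

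**What to change.** First, reconcile section 2.5 with sections 2.1, 2.2 and 2.11, so that the Phase 1 primary is either the collapsed comparison or the two stratum-specific co-primaries, with the Holm sentence made to match.

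Then restate section 2.10:

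- Tie the 80% to the collapsed comparison of 78 per arm, and say explicitly that it assumes a standardised effect of about 0.45 on a common MADRS/HAM-A score, in the anxiety stratum as well.
- Report the stratum-specific MADRS comparison as 39 per arm, with about 51% power at 0.05 and 39% at 0.025, and a detectable difference of 7.1 to 7.8 points.
- If the stratum-specific co-primaries are kept as confirmatory with 80% power for MADRS, state the size this needs within the depression stratum (step 5 of the working). Do not claim without condition that 156 is enough.

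The cost is wording in the protocol, registry entry and analysis plan. Recruitment is not expected before the fourth quarter of 2026, so this can be done in time. The downside is that the stated power becomes less favourable. Keeping confirmatory stratum-specific tests at 80% would also mean a larger Phase 1.
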